## Abstract

**Background:**

Acute Stanford type A aortic dissection (TAAD) is a life-threatening condition. Surgery is usually performed as a salvage procedure and is associated with significant postoperative early mortality and morbidity. Understanding the patient’s conditions and treatment strategies which are associated with these adverse events is essential for an appropriate management of acute TAAD.

**Methods:**

Nineteen centers of cardiac surgery from seven European countries have collaborated to create a multicentre observational registry (ERTAAD), which will enroll consecutive patients who underwent surgery for acute TAAD from January 2005 to March 2021. Analysis of the impact of patient’s comorbidities, conditions at referral, surgical strategies and perioperative treatment on the early and late adverse events will be performed. The investigators have developed a classification of the urgency of the procedure based on the severity of preoperative hemodynamic conditions and malperfusion secondary to acute TAAD. The primary clinical outcomes will be in-hospital mortality, late mortality and reoperations on the aorta. Secondary outcomes will be stroke, acute kidney injury, surgical site infection, reoperation for bleeding, blood transfusion and length of stay in the intensive care unit.

**Discussion:**

The analysis of this multicentre registry will allow conclusive results on the prognostic importance of critical preoperative conditions and the value of different treatment strategies to reduce the risk of early adverse events after surgery for acute TAAD. This registry is expected to provide insights into the long-term durability of different strategies of surgical repair for TAAD.

**Trial registration:**

ClinicalTrials.gov Identifier: NCT04831073.

## Background

Acute Stanford type A aortic dissection (TAAD) is a life-threatening condition. Surgery is usually performed as a salvage procedure and is associated with increased postoperative early mortality and morbidity [1]. Although early mortality has declined during the last years [2], the recent The Nordic Consortium for Acute Type A Aortic Dissection registry including 1189 patients operated from 2005 to 2015 in 8 centers showed that 30-day mortality after surgery for acute TAAD was as high as 18% [3]. The multicentre, prospective German Registry for Acute Aortic Dissection type A including 2137 TAAD patients operated from 2006 and 2010 documented a 30-day mortality of 16.9% [4]. A more recent analysis of the Society of Thoracic Surgeon database including 7353 patients operated from 2014 and 2017 for acute TAAD reported a 30-day mortality of 17% [5]. Furthermore, surgery for TAAD is often complicated by major adverse events such as stroke [5] and acute kidney failure [6], which may have a significant impact on late survival. In this scenario of significant postoperative mortality and morbidity, surgeon faces the controversial issue of the extent of surgical repair for acute TAAD by avoiding a major surgical repair, which may increase the risk of early adverse events, and by resecting segments of the aorta which otherwise may expose the patient to the risk of late aortic-related complications [7, 8]. Understanding the balance between the patient’s conditions which may not allow extensive procedure and those treatment strategies which may limit the risk of late adverse events in patients who remain alive long after the surgery is essential for an appropriate management of TAAD. However, previous registries [1, 3] did not provide information on the long-term durability of these procedures. We have planned the multicenter European registry of surgery for acute TAAD (ERTAAD) to evaluate the contemporary early outcomes and the durability of different surgical strategies for acute TAAD at 15 years in a large study population.

## Methods

The ERTAAD is an observational registry including patients who underwent surgery for acute TAAD at 19 centers of cardiac surgery located in seven European countries (Belgium, Czech Republic, Finland, France, Germany, Italy and the United Kingdom) (Table 1) from January 1, 2005 to March 31, 2021. Data will be retrospectively collected on patients treated during the study period and the aim is to gather further data for future clinical research on this topic. Data on consecutive patients with acute TAAD will be collected into a Microsoft Access datasheet (Redmond, Washington, USA) with pre-specified baseline, operative and outcome variables. Permission to conduct this study will be requested from institutional or national review boards according to local legislation.

**Table 1 Tab1:** Participating centers

Participating centers	
1. Ziekenhuis Oost-Limburg, Genk, Belgium	
2. Saint-Luc’s Hospital, Brussels, Belgium	
3. Sint-Jan Hospital, Bruges, Belgium	
4. Antwerp University Hospital, Edegem, Belgium	
5. University Hospitals Leuven, Leuven, Belgium	
6. Institute of Clinical and Experimental Medicine, Prague, Czech Republic	
7. Helsinki University Hospital, Helsinki, Finland	
8. Jean Minjoz University Hospital, Besançon, France	
9. Hôpital Henri Mondor, Assistance Publique - Hôpitaux de Paris, Créteil, France	
10. Leipzig Heart Center, Leipzig, Germany	
11. University Heart and Vascular Centre Hamburg, Hamburg, Germany	
12. Münster University Hospital, Münster, Germany	
13. University of Turin, Turin, Italy	
14. University of Verona Medical School, Verona, Italy	
15. University of Udine, Udine, Italy	
16. Glenfield Hospital, University Hospitals of Leicester, Leicester, UK	
17. Liverpool Heart and Chest Hospital, Liverpool, UK	
18. Sheffield Teaching Hospital, Sheffield, UK	
19. Southampton University Hospital, Southampton, UK	

### Inclusion criteria

TAAD or intramural hematoma involving the ascending aorta;Patients aged > 18 years:Symptoms started within 7 days from surgery;Primary surgical repair of acute TAAD;Any other major cardiac surgical procedure concomitant with surgery for TAAD.

### Exclusion criteria

Patients aged < 18 years;Onset of symptoms > 7 days from surgery;Prior procedure for TAAD;Retrograde TAAD (with primary tear located in the descending aorta);Concomitant endocarditis;TAAD secondary to blunt or penetrating chest trauma.

## Clinical and operative variables and their definition criteria

### Individual surgeon’s experience

Surgeon having performed performing at least 20 elective or urgent procedures on the ascending aorta/aortic arch in the preceding year.

### Baseline and postoperative laboratory parameters

Baseline levels of hemoglobin, creatinine, platelets, arterial lactate, cardiac enzymes and C-reactive protein as well as postoperative lowest levels of hemoglobin and platelets and postoperative peak levels of creatinine and arterial lactate will be collected.

### Preoperative antithrombotic drugs

Exposure to any of the following antithrombotic drugs within 2 days before surgery: aspirin, clopidogrel, ticagrelor, prasugrel, ticlopidine, low-molecular weight heparin, unfractionated heparin, fondaparinux, direct oral anticoagulants and/or warfarin.

### Renal function

Renal function will be classified according to the estimated glomerular filtration rate (eGFR) calculated using the Chronic Kidney Disease Epidemiology Collaboration (CKD-EPI) equation [9] and the European Kidney Function Consortium (EKFC) equation [10]. The severity of renal failure will be classified in different stages as listed in Table 2.

**Table 2 Tab2:** Stages of chronic kidney disease

Stages	eGFR (mL/min/1.73 m^**2**^)
1	≥90
2	60–89
3a	45–59
3b	30–44
4	15–29
5	< 15 or dialysis

*eGFR* estimated glomerular filtration rate

### Genetic syndromes

Genetic syndromes may lead to aortopathies and TAAD [11]. Information on any specific genetic syndrome associated with TAAD will be collected in this registry.

### Arterial hypertension

Systemic arterial pressure > 150/80 mmHg or use of antihypertensive drugs.

### Diabetes

Hyperglycemia requiring treatment with insulin or oral drugs.

### Prior stroke

Any preoperative focal or global neurological syndrome caused by ischemia or hemorrhage not resolving within 24 h. It refers to a neurological event occurring any time before hospitalization for TAAD, but not to a neurological event related to acute TAAD.

### Prior transient ischemic attack

Any preoperative focal or global neurological syndrome caused by ischemia or hemorrhage resolving within 24 h. It refers to a neurological event occurring any time before hospitalization for TAAD, but not to a neurological event related to acute TAAD.

### Pulmonary disease

Use of bronchodilators and/or steroids for lung diseases [12].

### Extracardiac arteriopathy

One or more of the following: lower limb claudication, critical limb ischemia, carotid occlusion or > 50% stenosis, major amputation for arterial disease, previous or planned intervention on the abdominal aorta or on the extremities or carotid arteries [12].

### Poor mobility

Severe impairment of mobility due to musculoskeletal or neurological dysfunction [12].

### Moderate-to-severe frailty

Patient needs assistance because of moderate-to-severe physical and cognitive impairment (score > 5 on the Rockwood Clinical Frailty Scale) [13].

### New York Heart Association functional classes

Functional classes according to the New York Heart Association classification whose definition criteria are summarized in Table 3 [14].

**Table 3 Tab3:** New York Heart Association functional classes

Class	Patient symptoms
I	No limitation of physical activity. Ordinary physical activity does not cause undue fatigue, palpitation, dyspnea, or anginal pain.
II	Slight limitation of physical activity. Comfortable at rest. Ordinary physical activity results in fatigue, palpitation, dyspnea or anginal pain.
III	Marked limitation of physical activity. Comfortable at rest. Less than ordinary activity causes fatigue, palpitation, dyspnea or anginal pain.
IV	Inability to carry on any physical activity without discomfort. Symptoms of heart failure or the anginal syndrome may be present even at rest. If any physical activity is undertaken, discomfort is increased.

### Recent myocardial infarction

Myocardial infarction within 90 days from the index surgery [12]. It includes acute coronary malperfusion (i.e. any changes in ST level in electrocardiogram and/or an increase in cardiac enzymes).

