### Malperfusion

Malperfusion refers to acute organ ischemia secondary to aortic branch vessel hypoperfusion. This severe condition is usually classified based on clinical signs and symptoms [15, 16]. Herein, myocardial malperfusion will be defined as any changes in ST level in electrocardiogram and/or an increase in cardiac enzymes. Cerebral malperfusion will be defined as acute preoperative stroke. Spinal malperfusion will be defined as acute paraparesis/paraplegia. Mesenteric malperfusion will be as sudden, mild-to-severe abdominal pain with or without nausea and vomiting, which is accompanied or not by rectal bleeding or bloody diarrhea [17]. Renal malperfusion will be defined as anuria/oliguria. Peripheral malperfusion will be defined as loss of pulse with or without sensory or motor deficits of any limb.

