## Statistical analysis

Statistical analyses will be conducted using Stata v. 15.1 (StataCorp LLC, Texas, USA) and SPSS v. 27.0 (IBM Corporation, Armonk, NY, USA) statistical softwares. Continuous variables and outcomes will be reported as mean and standard deviation as well as median and interquartile range. Categorical variables and outcomes will be reported as counts and percentages. A *p* < 0.05 will be set for statistical significance. Differences between the study groups will be evaluated using the Fisher’s exact test, the Chi-square test, the linear-by-linear association test, the Mann-Whitney test and the Kruskall-Wallis test. The McNemar test and paired samples T-test will be used in the paired groups. Propensity score matching will be performed to balance treatment strategies for baseline differences. A propensity score will be estimated using a non-parsimonious multilevel mixed-effects logistic regression considering the cluster effect of the participating centers whose results may be affected by the referral pathway, surgical techniques and perioperative care. Multilevel mixed-effects logistic regression model will include all available baseline variables. The estimated propensity score will be employed for inverse propensity score weighting analysis and one-to-one propensity score matching analysis using a caliper width of 0.1 to 0.2 of the standard deviation of the estimated logit. Standardized differences < 0.10 will be considered an acceptable imbalance between the matched cohorts.

Survival analysis will be performed using the Kaplan-Meier method with the log-rank test and the Cox proportional hazards method. Competing risk analysis with the Gray’s test will be performed for late non-fatal adverse events because patient’s death might hinder the observation of these events. Regression models will include covariates with *p* < 0.05 or *p* < 0.2 in univariate analysis according to the number of covariates of interest. Risk estimates will reported as hazard ratios and subdistribution hazard ratios with their 95% confidence intervals.

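### Recent myocardial infarction contains myocardial malperfusion by identical criteria, so in a model with both the malperfusion coefficient changes meaning and is poorly estimated

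*Protocol article*

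**What the plan says.** Under Recent myocardial infarction, the protocol article sets a window of 90 days before the index surgery and then extends the variable: "It includes acute coronary malperfusion (i.e. any changes in ST level in electrocardiogram and/or an increase in cardiac enzymes". Under Malperfusion it states that "myocardial malperfusion will be defined as any changes in ST level in electrocardiogram and/or an increase in cardiac enzymes". The two sets of criteria are the same.

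For the brain the article does the reverse. Prior stroke covers events at any time before the hospitalization, "but not to a neurological event related to acute TAAD", and prior transient ischemic attack carries the same exclusion. Acute preoperative stroke is coded as cerebral malperfusion.

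The Statistical analysis section gives three routes into a model:

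- **Propensity score:** "Multilevel mixed-effects logistic regression model will include all available baseline variables".
- **Survival and competing-risk regressions:** "Regression models will include covariates with" a univariate p below 0.05 or 0.2, depending on how many covariates are of interest.
- **Early adverse events and the risk score:** logistic and linear regression with and without stepwise selection. For the score, variables are kept if chosen in at least half of 100 stepwise runs, each on 70% of a 75% derivation set, and further covariates are added by the Akaike criterion.

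The article does not say what happens when recent MI and myocardial malperfusion are both candidates.

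**The concern.** Every patient with myocardial malperfusion is, by definition, also a patient with recent MI. The only patients who separate the two variables are those with a recent infarction unrelated to the dissection, and these may be few.

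This bears on a stated aim. The abstract promises conclusions on the prognostic importance of critical preoperative conditions, and malperfusion is part of the registry's own urgency classification. Both variables are candidates for the models meant to find independent risk factors. If both enter, a reader will take the malperfusion odds ratio as malperfusion versus no event, which it is not. If selection keeps only recent MI, an acute complication of the dissection is reported under the name of a comorbidity.

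**Working it through.** The documents give no figure that depends on these definitions, so there is nothing to reproduce. The check is what a joint model estimates.

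**Cells.** Let R be recent MI and M myocardial malperfusion. The definitions allow three cells: (a) neither, R=0, M=0; (b) other recent MI, R=1, M=0; (c) malperfusion, R=1, M=1. With logit p = α + β_R·R + β_M·M:

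- β_R = logit p_b − logit p_a
- β_M = logit p_c − logit p_b
- β_R + β_M = logit p_c − logit p_a

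So exp(β_M) is the odds ratio of malperfusion versus neither, divided by that of other recent MI versus neither. The effect against no event is the sum of the two coefficients.

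**Inputs.** N = 6000 is the registry size expected in the Sample size calculation section. The rest is assumed, because the documents give no values: malperfusion 10%, other recent MI 0.5% or 2%, reference risk p_a = 0.16, odds ratio of malperfusion versus neither 2.5. The model has no other covariates.

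**Standard errors.** As defined: SE = √[1/(n_c p_c(1−p_c)) + 1/(n_b p_b(1−p_b))]. With disjoint coding, cell a replaces cell b.

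Worked case, other recent MI 2% with odds ratio 1.5:

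- p_c = 0.323, n_c = 600, so 1/(600×0.323×0.677) = 0.0076
- p_b = 0.222, n_b = 120, so 1/(120×0.222×0.778) = 0.0482
- n_a = 5280, so 1/(5280×0.16×0.84) = 0.0014
- As defined: odds ratio 2.5/1.5 = 1.67, SE = √0.0558 = 0.236
- Disjoint: odds ratio 2.50, SE = √0.0090 = 0.095

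| Odds ratio of other recent MI | Malperfusion odds ratio in joint model | SE, other MI 2% | SE, other MI 0.5% |
|---|---|---|---|
| 0.7 | 3.57 | 0.296 | 0.573 |
| 1.0 | 2.50 | 0.264 | 0.506 |
| 1.5 | 1.67 | 0.236 | 0.448 |
| 2.5 | 1.00 | 0.214 | 0.400 |
| 3.5 | 0.71 | 0.206 | 0.383 |

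The disjoint SE is 0.095 throughout, so the loss is roughly two- to six-fold. If other recent MI were only 0.2% (12 patients), the SE would be larger still: from √(0.0076 + 1/(12×0.40×0.60)) = 0.60 at odds ratio 3.5, to √(0.0076 + 1/(12×0.118×0.882)) = 0.90 at 0.7. The two coefficients combine to an odds ratio of 2.50 in every row. A logistic fit to 2 million simulated records (10% and 2%) gave 3.59, 2.52 and 1.65 for the first three rows.

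**Correlation.** With prevalences m for M and q for R, r = m(1−q)/√[m(1−m)q(1−q)]. At 10% and 12% this is 0.088/√(0.09×0.1056) = 0.90, a variance inflation factor of 1/(1−r²) = 5.4. Over malperfusion 5–15% and other recent MI 0.2–2%, r is 0.84–0.99 and the factor 3.3–65.

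**Selection.** Each bootstrap sample has 6000×0.75×0.70 = 3150 patients, of whom 16 (0.5%) to 63 (2%) have other recent MI. They alone decide between the two variables. In the worked case the SE scales by √(6000/3150) = 1.38 to 0.326. With both in the model, malperfusion then has z = ln(1.67)/0.326 = 1.57, short of the 1.96 that the 0.05 stay rule needs. Under disjoint coding z = ln(2.5)/(0.095×1.38) = 7.0.

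**The case against.** The strongest reply is that little of this damages the results.

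- **Which models hold both.** Only the propensity model is committed to both variables. Its coefficients are not interpreted, and collinearity hardly alters the fitted score. Outcome models may hold both but need not. This stands and limits the point to models whose coefficients are read as risk factors.
- **Prediction.** The two coefficients sum correctly, so predicted risk is unaffected. If malperfusion is dropped, recent MI carries most of the signal: with an assumed 10% malperfusion (odds ratio 2.5), 4% other recent MI (1.8) and 16% reference risk, recent MI alone has an odds ratio of about 2.29. This also stands. The harm is to interpretation and naming.
- **Intent.** The recent MI item cites the same source as several other comorbidity items, and comparison with current risk scores is planned, so the wide definition may be deliberate. That source is not at hand, so this cannot be settled. It would justify the wide item for that score, not for the registry's own models.
- **The stroke contrast.** A history item and a 90-day item ending at surgery are different constructs, so the sections do not contradict each other. Agreed: the contrast shows only that the article already has a workable rule for separating the acute event.
- **Repair at analysis.** Malperfusion is defined separately, so a disjoint variable can largely be derived later. That makes the fix cheap. But the overlap is a stated rule, not a detail left out of the article.

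A reader might infer that malperfusion is understated in any model with both. The documents do not support that. The direction depends on the effect of other recent MI, which they do not give, and the table shows understatement, no bias and overstatement in turn.

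**Conclusion.** The point holds in limited form. One acute cardiac event is coded in two nested baseline variables. Wherever both enter an outcome or risk-factor model, the malperfusion coefficient is its effect relative to other recent MI.

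The change of meaning follows from the definitions alone. The size of the precision loss rests on the assumed prevalences, effects and reference risk, and holds as long as other recent MI is much rarer than having neither condition. The direction of any bias is open: downward only if other recent MI itself raises risk. Unstable selection follows from the small group that separates the two variables. The propensity score and predicted risk are largely untouched. The definition should be changed before the risk-factor models are run, but it does not threaten the registry's main comparisons.

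**What to change.** For the registry's own risk-factor and score-development models, code recent MI as infarction within 90 days that is not related to the index dissection, as is already done for prior stroke and transient ischemic attack. Code acute ST or enzyme changes only as myocardial malperfusion. Alternatively, keep both definitions and state that the two variables never enter the same model. Where an existing risk score needs the wider item, derive it as the union of the two for that score only.

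The cost is one sentence in the variable definition and a recode, since malperfusion already has its own definition as a variable. Records with unclear timing, or with both an earlier infarction and acute malperfusion, need checking.

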### Pulmonary hypertension

Systolic pulmonary artery pressure on arrival in the operating room classified in three categories: < 31 mmHg, 31–55 mmHg and > 55 mmHg [12].

### Critical preoperative state

Ventricular tachycardia or ventricular fibrillation or aborted sudden death, preoperative cardiac massage, preoperative ventilation before anesthetic room, preoperative inotropes, preoperative acute renal failure (anuria or oliguria < 10 ml/hr) [12]. These conditions will be reported as separate variables.

### Urgency of the procedure

Urgency of the procedure will be classified in five categories based on increasing severity of hemodynamic instability and the need and timing of cardiopulmonary resuscitation (Table 4).

**Table 4 Tab4:** Urgency of the procedure.*

Urgency	Definition
Urgent	Scheduled procedure performed in paucisymptomatic patients with stable hemodynamic conditions during the index hospitalization since the next working day from admission
Emergency grade 1	Procedure performed in patients with stable conditions and without malperfusion before the beginning of the next working day
Emergency grade 2	Procedure performed in patients with hemodynamic instability despite the use of inotropes and/or any malperfusion before the beginning of the next working day - no cardiopulmonary resuscitation with chest compression required
Salvage grade 1	Procedure performed in patients requiring cardiopulmonary resuscitation with external chest compressions and/or open chest cardiac massage between induction of anesthesia and initiation of cardiopulmonary bypass
Salvage grade 2	Procedure performed in patients requiring cardiopulmonary resuscitation with external chest compressions en route to the operating theatre or before induction of anesthesia

Further details on the definition criteria of the urgency of the procedure are reported in the text

Urgent procedure refers to a procedure which was scheduled for the next working day from admission or later during the index hospitalization. These patients were hemodynamically stable and paucisymptomatic. In these patients, TAAD was considered not to cause to malperfusion and/or aortic rupture within the next few hours/days.

Emergency grade 1 refers to any procedure which was performed before the beginning of the next working day in symptomatic or paucisymptomatic patients with stable hemodynamic conditions and without signs of malperfusion. The procedure was performed within a few hours after admission to the hospital.

Emergency grade 2 refers to any procedure which was performed before the beginning of the next working day because of hemodynamic instability despite the use of inotropes and/or of malperfusion. These patients did not require cardiopulmonary resuscitation. The procedure was performed immediately after admission to the hospital or worsening of the patients’ conditions.

Salvage grade 1 refers to any procedure which was performed in patients requiring cardiopulmonary resuscitation with external chest compressions and/or open cardiac massage between induction of anesthesia and initiation of cardiopulmonary bypass. The procedure was performed when the conditions of the patients worsened after induction anesthesia due to acute heart failure, cardiac tamponade and/or frank rupture of the aorta. These patients required either external chest compressions before sternotomy and/or cardiac massage after sternotomy and prompt initiation of cardiopulmonary bypass.

Salvage grade 2 refers to any procedure which was performed in patients requiring cardiopulmonary resuscitation with external chest compressions en route to the operating theatre or prior to induction of anesthesia. These patients might have required also cardiac massage after sternotomy and prompt initiation of cardiopulmonary bypass. In these patients, the operation was performed on compassionate basis without knowledge of frank rupture of the aorta or severe end-organ injury.

